**Fig. 1 f0005:**
[figure not shown]
Flow chart for the clinical trial.

Should the status of a participant deteriorate, as identified using weekly measures with the Patient Health Questionnaire (PHQ-9), the secure platform will notify her assigned therapist about the matter, who then contacts the individual for further help or referral. Unless vital to refer to another healthcare provider, the participant can remain in treatment. The principal investigators (MB and AR) will assume overall responsibility for clinical issues concerning the participants.

### Inclusion and exclusion criteria

2.2

Individuals interested in participating in the clinical trial are self-referred on the basis of recognizing perfectionism as an ongoing concern. In order to determine eligibility, a set of inclusion and exclusion criteria will be applied; 1) ≥18 years of age 2) adequate reading and writing levels in Swedish 3) a computer, smartphone, or tablet with Internet access, and 4) elevated levels of perfectionism, as determined by a score of >29 on the subscale Concerns over Mistakes on the Frost Multidimensional Perfectionism Scale (FMPS; Frost et al., 1990). Diagnoses are not a reason for exclusion unless they require more immediate care, e.g., anorexia nervosa, substance abuse, bipolar disorder, psychosis, and schizophrenia, as assessed during the telephone interview. Those who display severe depression or suicidality during screening will be contacted and referred to their local healthcare provider, as determined by a score of >15 or > 2 points on the item on suicidal ideation on the PHQ-9 (Kroenke et al., 2001). Excluded individuals will not be able to take part in treatment.

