
The clinical trial will thus test two treatments for perfectionism over eight weeks, and will be delivered to self-referred participants who are recruited on the basis of experiencing perfectionism as a major concern. Both will be administered via the Internet in order to replicate prior studies of the same mean of delivery. Given that no investigation has previously tested the effects of iUP for perfectionism, no hypothesis regarding, for instance, superiority is possible to provide. However, because iCBT-P was developed specifically for targeting perfectionism, it is assumed to have a greater impact on this particular issue. The clinical trial will involve the following research questions; 1) what are the effects on self-rated perfectionism and psychiatric symptoms of an eight-week Internet-delivered treatment with guidance on demand (iCBT-P)? 2) what are the effects on the same outcomes for iUP? 3) to what extent has treatment affected other domains, such as relationships, as measured using subjective ratings? 4) how are the treatments experienced by the participants themselves, as explored using qualitative interviews?

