### Participants and procedure

2.1

Participants will be recruited via advertisements and social media. Those who identify themselves as perfectionists will be referred to a website that has been created specifically for the purpose of the clinical trial. This mean of recruitment has effectively been used before for issues that are not considered to be diagnoses (Rozental et al., 2017), and has the advantage of reaching individuals who themselves regard perfectionism as problematic. The website will consist of general information about the study, the researchers and therapists, ethical issues, and the conditions for their participation. Once an individual signs up to participate, she enters a secure platform using an autogenerated username, e.g., 1234abcd, strong personal password, and six-letter code sent out as a SMS (for more details, see Vlaescu et al., 2016). This type of authorization process is used by many authorities and is regarded to be safe for sharing sensitive data. When the individual is logged on, she then completes a number of questions of demographic nature and all of the self-report measures listed below. These are used to determine eligibility to be included. Those who meet inclusion criteria are later interviewed via telephone using the Mini-International Neuropsychiatric Interview version 7.0 to confirm diagnoses and screen for conditions that are considered a reason for exclusion (MINI; Lecrubier et al., 1997).

Following recruitment, all included participants are randomized by an independent individual not involved in the study. Randomization will be done to the two conditions according to a 1:1 ratio and using a random numbers generator (www.random.org). Treatment content, communication with therapists, technical support, and all self-report measures can be accessible through the secure platform, using the same type of login as described above. Participants will connect their own emails to their autogenerated username, however only notices to log on to the secure platform will be sent out. The treatments are both eight weeks long, after which the participants complete the same type of self-report measures as before (two of them will also be filled out weekly throughout treatment), with a similar procedure being applied at six and 12 months following treatment completion, see Fig. 1 for an overview.

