### Self-report measures

2.4

The clinical trial will include two main outcomes concerning the levels of perfectionism among the participants; the Clinical Perfectionism Questionnaire (CPQ; Fairburn et al., 2003), and the FMPS (Frost et al., 1990). The CPQ consists of 12 items that are scored on a four-point Likert-scale 1–4 (“Not at all” to “All of the time”), with two items that are in reverse (items 2 and 8), and employing a time-frame of one month to increase its clinical usefulness. The CPQ was translated to Swedish in a previous clinical trial, demonstrating good convergent and discriminant validity when compared to self-report measures of perfectionism and psychiatric symptoms, as well as adequate internal consistency (α = .68) and test-retest reliability (*r* = .62) (McMahan et al., submitted). The FMPS is scored on a five-point Likert-scale 1–5 (“Strongly disagree” to “Strongly agree”), with a total of 35 items that cover the six separate subscales Concern over Mistakes, Personal Standards, Doubts about Action, Parental Expectations, Parental Criticism, and Organization. However, only the first two are usually of interest in clinical trials as the other subscales are considered less related to the two higher-order dimensions of perfectionism (Limburg et al., 2017). The subscales of the FMPS has adequate to excellent internal consistencies (.88 and .83) and exhibits convergent and discriminant validity when compared to self-report measures of perfectionism and psychiatric symptoms (Purdon et al., 1999). The FMPS was originally translated to Swedish by Lundh et al. (1994). Apart from completing the two main outcomes during screening and at post-treatment and follow-up, participants will also fill out the CPQ weekly during treatment, see Table 1 for an overview.

**Table 1 t0005:** Overview of the self-report measures.

Self-report measure	Assessment											
	Screening	1	2	3	4	5	6	7	8	Post	6 months	12 months
CPQ	X	X	X	X	X	X	X	X	X	X	X	X
FMPS	X									X	X	X
PHQ-9	X	X	X	X	X	X	X	X	X	X	X	X
GAD-7	X									X	X	X
BBQ	X									X	X	X
SCS-SF	X									X	X	X
PPS	X									X	X	X
PSS	X									X	X	X
Credibility			X									
Domains^a^	X									X	X	X
Goals^b^	X									X	X	X
NEQ										X		

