### Statistical analysis

2.8

In the literature, no prior estimates are available for a power calculation when it comes to what constitutes a reasonable between-group effect size in terms of perfectionism. However, it is reasonable to assume a moderate standardized difference when comparing iCBT-P and iUP on the CPQ in favor of the former. This is based on the assumption that iCBT-P was developed specifically to target perfectionism. Thus, using G*Power to determine the sample size required to detect a Cohen's *d* of 0.50 (α of .05 and β of 0.80) suggest that 64 participants per condition (*n* = 128) will be required for the study. As for the within-group effect size for each condition between screening and post-treatment, the power achieved under these circumstances reveal that it will be possible to detect an effect size *d* of 0.36. The prior study by Zetterberg et al. (2019) demonstrated an effect size *d* of 1.19 on the CPQ for participants receiving iCBT-P with guidance on demand, and > 0.49 for all of the secondary outcomes, which indicates that the current clinical trial should be able to detect a difference on each of the self-report measures.

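### Within-arm change on FMPS Concern over Mistakes is inflated by regression to the mean, because the screening score that admits participants is also its only pre-treatment value

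*Protocol article*

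**What the plan says.** All references are to the protocol article.

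- Section 2.2 (Inclusion and exclusion criteria) requires "elevated levels of perfectionism, as determined by a score of >29 on the subscale Concerns over Mistakes" of the FMPS.
- Section 2.1 (Participants and procedure) says of the measures completed at sign-up: "These are used to determine eligibility to be included". Randomisation comes later: "Following recruitment, all included participants are randomized by an independent individual not involved in the study".
- Section 2.4 (Self-report measures): "The clinical trial will include two main outcomes concerning the levels of perfectionism among the participants". These are the CPQ and the FMPS. On timing: "Apart from completing the two main outcomes during screening and at post-treatment and follow-up, participants will also fill out the CPQ weekly during treatment". Table 1 agrees: the FMPS has a mark at screening, post-treatment, 6 months and 12 months, and nowhere else.
- Section 1.2 poses the first two research questions one treatment at a time. Question 1 asks about the effects of iCBT-P, and question 2 asks "what are the effects on the same outcomes for iUP".
- Section 2.8 (Statistical analysis) introduces the detectable within-condition effect with the words "As for the within-group effect size for each condition between screening and post-treatment" and plans standardised effect sizes both within and between conditions. The FMPS goes into a repeated measures analysis of variance.
- Both arms receive active treatment. The limitations in the Discussion do not mention regression to the mean.

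**The concern.** A score just above a cut-off is partly a stable level and partly measurement error or a temporary high. Selecting on the score selects on both parts, and the second does not persist. Unless the retest correlation is 1, the selected group's mean falls at the next measurement with no treatment at all. The article's description of perfectionism as trait-like does not remove this, because the fall comes from the unstable part of the score.

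Here the selecting score is the starting point of every FMPS change. Questions 1 and 2 ask for the effect of each treatment by itself, and no untreated arm shows how far scores would have fallen anyway. What is at stake is the within-arm effect size for Concern over Mistakes at post-treatment and at both follow-ups. Table 1 fixes the measurement schedule, so a later analysis plan could not supply the missing value.

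**Working it through.** **The plan's own figures.** For d = 0.50, two-sided α = 0.05 (two-sided is assumed) and 80% power, the t-test needs 64 per arm (power 0.801); the normal approximation gives 63. A paired t-test with n = 64 and 80% power detects d = 0.356, which rounds to the stated 0.36. Both figures reproduce.

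**Inputs.**
- Cut-off above 29 (section 2.2).
- Retest correlation r: none is given for the FMPS. Assumed range 0.62 to 0.88. The lower end is the CPQ retest value and the upper end the higher of the two FMPS internal consistencies (both section 2.4).
- Share p of applicants above the cut-off: not given. Assumed 50% to 90%.
- Applicant scores normal, with the same mean and SD at retest when untreated. Other eligibility rules are ignored.

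**Formulas**, in units of the applicant SD, where c is the standard normal point with share p above it:
- L = φ(c)/p, the mean of those selected
- expected fall = (1 − r) × L
- variance of selected screening scores V = 1 + cL − L²
- d on the screening SD of those included = fall/√V
- SD of change = √[(1 − r)²V + 1 − r²]

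**Middle case, r = 0.75, p = 0.70.** c = −0.524, φ(c) = 0.348, L = 0.348/0.70 = 0.497.
- Fall = 0.25 × 0.497 = 0.124.
- V = 1 − 0.260 − 0.247 = 0.493, so √V = 0.702 and d = 0.124/0.702 = 0.177.
- SD of change = √(0.0625 × 0.493 + 0.4375) = 0.684, so the paired-scale effect is 0.124/0.684 = 0.181. With n = 64 the paired test then rejects with probability about 0.30.

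**Range.** Expected fall, d, and chance that a one-arm paired test (n = 64) rejects, all with zero treatment effect:

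| r | pass rate | fall (applicant SD) | d (screening SD of included) | rejection |
|---|---|---|---|---|
| 0.62 | 50% | 0.303 | 0.503 | 0.83 |
| 0.62 | 70% | 0.189 | 0.269 | 0.43 |
| 0.62 | 90% | 0.074 | 0.088 | 0.10 |
| 0.75 | 50% | 0.199 | 0.331 | 0.64 |
| 0.75 | 70% | 0.124 | 0.177 | 0.30 |
| 0.75 | 90% | 0.049 | 0.058 | 0.08 |
| 0.88 | 50% | 0.096 | 0.159 | 0.35 |
| 0.88 | 70% | 0.060 | 0.085 | 0.16 |
| 0.88 | 90% | 0.023 | 0.028 | 0.06 |

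**Simulation of the middle case**, 4,000 trials without a treatment effect, 64 per arm. The mean within-arm fall was 0.124 applicant SD, and the one-arm paired test rejected in 29.2% of trials. The difference between arms averaged 0.001 SD, with a type I error of 4.6%.

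**The case against.** The strongest reply is that the trial is randomised. Both arms pass the same cut-off, so the fall is equal in expectation and cancels in the comparison. The simulation confirms this. The sample size rests on a between-arm CPQ difference, and recovery is defined on the CPQ, so neither is directly affected. All of this stands. It does not answer questions 1 and 2, which are put for each treatment separately, and within-condition effect sizes are planned. The Discussion also says that the trial is not designed to test superiority.

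A second reply is that the size is unknown and may be small. This stands too. Applicants refer themselves because they see themselves as perfectionists, so a high pass rate is plausible. At 90% passing, d is only 0.03 to 0.09. The value 0.62 is borrowed from the CPQ, whose internal consistency (.68) is lower than that of the FMPS subscales (.88 and .83).

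A reader might infer four stronger things that the article does not support:

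- *That regression alone reaches the 0.36 called detectable.* The 0.36 is on the paired scale (SD of change), whereas the d values above use the narrowed screening SD. On the paired scale the assumed range runs from 0.05 to 0.37, and only the most extreme corner (r = 0.62, 50% passing) reaches 0.36.
- *That the narrowed baseline SD certainly inflates d further.* Section 2.8 does not name the SD. With a pooled pre/post SD the range is 0.03 to 0.41.
- *That drift between screening and treatment start adds to the bias.* The article states no interval and gives no evidence of drift in one direction. Its timeline (recruitment in September, eight weeks of treatment completed in November) limits the gap to about five weeks.
- *That every outcome is affected alike.* Personal Standards and the CPQ are affected only through their correlation with the selected score.

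**Conclusion.** The point holds for within-arm change on FMPS Concern over Mistakes, at post-treatment and both follow-ups, in both arms. The direction is certain for any retest correlation below 1. The size rests on assumptions: d of about 0.03 to 0.50 on the screening SD of the included sample for r from 0.62 to 0.88 and 50% to 90% passing, and about 0.18 in the middle case.

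The randomised comparison of iCBT-P with iUP is not biased, and nothing here casts doubt on it. Nor does the artefact invalidate within-arm results as a whole. It is unlikely to explain all of a large pre-post effect such as the d of 1.19 that section 2.8 cites for the CPQ. This is a cheap improvement and not a fatal flaw.

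**What to change.** 1. Re-administer the FMPS on the platform after eligibility is confirmed and just before randomisation, and add the column to Table 1. Randomisation already follows recruitment, so there is a natural place for it.
2. In section 2.8, make this second value the baseline for FMPS change and for within-group FMPS effect sizes. Keep the screening score for eligibility only, and do not apply the cut-off again to the second value, which would reintroduce the selection. This takes most of the regression out of the pre-post estimate.
3. State that within-arm change cannot be attributed to treatment alone, and give the between-arm estimate priority.

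The cost is one short extra online questionnaire for included participants, one column in Table 1 and a few sentences of text. Within-arm effect sizes will come out somewhat smaller. The other scales need not be repeated for this purpose. If the extra assessment cannot be added, step 3 can still be taken alone.

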### Withdrawal

2.3

Participants can withdraw from the clinical trial at any moment. The reason for this will be explored for research purposes, but the individual will be informed that she can defer from specifying her motive.

### Self-report measures

2.4

The clinical trial will include two main outcomes concerning the levels of perfectionism among the participants; the Clinical Perfectionism Questionnaire (CPQ; Fairburn et al., 2003), and the FMPS (Frost et al., 1990). The CPQ consists of 12 items that are scored on a four-point Likert-scale 1–4 (“Not at all” to “All of the time”), with two items that are in reverse (items 2 and 8), and employing a time-frame of one month to increase its clinical usefulness. The CPQ was translated to Swedish in a previous clinical trial, demonstrating good convergent and discriminant validity when compared to self-report measures of perfectionism and psychiatric symptoms, as well as adequate internal consistency (α = .68) and test-retest reliability (*r* = .62) (McMahan et al., submitted). The FMPS is scored on a five-point Likert-scale 1–5 (“Strongly disagree” to “Strongly agree”), with a total of 35 items that cover the six separate subscales Concern over Mistakes, Personal Standards, Doubts about Action, Parental Expectations, Parental Criticism, and Organization. However, only the first two are usually of interest in clinical trials as the other subscales are considered less related to the two higher-order dimensions of perfectionism (Limburg et al., 2017). The subscales of the FMPS has adequate to excellent internal consistencies (.88 and .83) and exhibits convergent and discriminant validity when compared to self-report measures of perfectionism and psychiatric symptoms (Purdon et al., 1999). The FMPS was originally translated to Swedish by Lundh et al. (1994). Apart from completing the two main outcomes during screening and at post-treatment and follow-up, participants will also fill out the CPQ weekly during treatment, see Table 1 for an overview.

**Table 1 t0005:** Overview of the self-report measures.

Self-report measure	Assessment											
	Screening	1	2	3	4	5	6	7	8	Post	6 months	12 months
CPQ	X	X	X	X	X	X	X	X	X	X	X	X
FMPS	X									X	X	X
PHQ-9	X	X	X	X	X	X	X	X	X	X	X	X
GAD-7	X									X	X	X
BBQ	X									X	X	X
SCS-SF	X									X	X	X
PPS	X									X	X	X
PSS	X									X	X	X
Credibility			X									
Domains^a^	X									X	X	X
Goals^b^	X									X	X	X
NEQ										X		

CPQ = Clinical Perfectionism Questionnaire; FMPS = Frost Multidimensional Perfectionism Scale; PHQ-9 = Patient Health Questionnaire; GAD-7 = Generalized Anxiety Disorder; BBQ = Brunnsviken Brief Quality of Life Scale; SCS-SF = Self-Compassion Scale - Short Form; PPS = Pure Procrastination Scale; PSS = Perceived Stress Scale; NEQ = Negative Effects Questionnaire.

a Interests/leisure, work/studies, friendships/social life, community engagement/spirituality, family life/parenting, rest/sleep, love/intimate relationships, and physical activity/diet.

b Goal attainment, as set and defined by the participants.

A number of secondary outcomes will also be included. The nine-item PHQ-9 assesses the degree of depression and is scored on a four-point Likert-scale 0–3 (“Not at all” to “Nearly every day”). The PHQ-9 is often used as a screening tool for depressive symptoms, has been validated against other self-report measures and clinical interviews of depression, and has an excellent internal consistency (.89) (Kroenke et al., 2001). The seven-item Generalized Anxiety Disorder (GAD-7) determines the level of anxiety and is scored on a four-point Likert-scale 0–3 (“Not at all” to “Nearly every day”). The GAD-7 is often used for screening for symptoms of anxiety and worry, corresponds well with other similar self-report measures, and has exhibited excellent internal consistency (.92) (Spitzer et al., 2006). The 12-item Brunnsviken Brief Quality of Life (BBQ) explores the quality of life in six areas, e.g., leisure and learning, and level of importance, e.g., “my leisure time is important to me”, which are then multiplied with each other. The BBQ is scored on a four-point scale 1–4 (“Strongly disagree” to “Strongly agree”), with a range in scores of 0–96. The BBQ demonstrates good convergent and discriminant validity, good classification ability, and has an adequate internal consistency (.76) (Lindner et al., 2016). The 12-item Self-Compassion Scale - Short Form (SCS-SF) tests the degree of self-compassion and is scored on a five-point scale 1–5 (“Almost never” to “Almost all of the time”). The SCS-SF has been shown to correlate with self-report measures of psychiatric symptoms, and has a good internal consistency (.86) (Raes et al., 2011). The 12-item Pure Procrastination Scale (PPS) determines the level of procrastination and is scored on a five-point Likert-scale 1–5 (“Seldom, or do not agree” to “Very often, or totally agree). The PPS has been shown to have good convergent and discriminant validity, and internal consistency (.78) (Rozental et al., 2014b; Steel, 2010). The 14-item Perceived Stress Scale (PSS) evaluates the subjective experience of general stress in various situations and is scored on a five-point Likert-scale 0–4 (“Never” to “Very often”), with seven items being scored in reverse (items 4–7, 9–10, and 13). The PSS has been shown to have good internal consistency (.84–.86) as well as good convergent and discriminant validity (Cohen et al., 1983). Lastly, the 32-item Negative Effects Questionnaire (NEQ) will be used to probe for unwanted and adverse events that might arise during treatment, which is scored on a five-point Likert-scale 0–4 (“Not at all” to “Extreme”), and classifies the incidents as caused by the treatment or other circumstances. The NEQ has demonstrated excellent internal consistency (.95) and is mainly used to descriptively determine the occurrence and nature of possible negative effects (Rozental et al., 2016). All of the listed secondary outcomes have previously been translated to Swedish. Moreover, with the exception of the PHQ-9, which is completed weekly during treatment, and the NEQ, which is only filled out at post-treatment, all self-report measures are completed during screening and at post-treatment and follow-up.

Furthermore, the perceived integrity of iCBT-P and iUP will be explored using the five-item Credibility/Expectancy Questionnaire (Borkovec and Nau, 1972), which is scored on a 10-point Likert-scale 0–10 (e.g., “Not at all logical” to “Very logical”). It has exhibited good internal consistency (.86–.90), with the factor expectancy being correlated with outcomes of treatment (Devilly and Borkovec, 2000). In addition, the effects of treatment will also be explored using subjective rvatings of their impact on different domains. This will entail eight aspects of life that each participant rates on a 10-point Likert-scale 0–10 with regard to how perfectionism is affecting them negatively (“Not at all” to “Very much”): interests/leisure, work/studies, friendships/social life, community engagement/spirituality, family life/parenting, rest/sleep, love/intimate relationships, and physical activity/diet. Participants will also define their own goals of treatment and to what extent they have lived up to them, also a 10-point Likert-scale 0–10.

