### Treating perfectionism

1.1

Perfectionism is regarded as a transdiagnostic phenomenon that can be problematic in itself, but that is also involved in processes that can create or maintain other psychiatric symptoms. This notion is confirmed by the fact that perfectionism is elevated in many conditions, that it predicts the onset and recovery from depression, and that it has strong links to, for example, obsessive-compulsive disorder and social anxiety disorder (Egan et al., 2011). Perfectionism can also affect the course of treatment for these conditions by leading to poorer therapeutic alliance, non-response, and drop-out, particularly with regard to the engagement with certain interventions, such as exposure to fearful stimuli or using behavioral activation (Egan et al., 2016). Hence, there are several reasons to be aware of perfectionism among patients as it can affect both adherence to treatment and result in worse prognostic outlook and increase the risk of relapse. For this reason, Shafran et al. (2002) proposed a cognitive-behavioral conceptualization of perfectionism that can help guide therapists in their assessment and treatment. This stems from their definition of perfectionism being characterized by tightly held inflexible standards, and intends to target cognitive biases and performance-related behaviors, such as via behavioral experiments. Four components were considered important: 1) providing psychoeducation about perfectionism and creating an individualized conceptualization 2) broadening the domains for self-evaluation 3) testing out beliefs and predictions, and 4) addressing personal standards and self-criticism. The treatment has been developed into a manual (Egan et al., 2016), and a self-help book (Shafran et al., 2018), which can be used either stand-alone or in relation to other evidence-based interventions when perfectionism is relevant to address.

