### Treatments and therapists

2.5

The clinical trial will randomly assign participants into one of two conditions; 1) iCBT-P, which is the manual developed by Egan et al. (2016) specifically for perfectionism, administered via the Internet, or 2) iUP, which is a transdiagnostic manual intended to target the shared emotional aspects that underlie depression and anxiety disorders, but here adapted to be Internet-delivered. Both treatments will be delivered in a similar manner over eight weeks, consisting of reading material, graphis, audio and video, and a number of exercises to be completed on the secure platform. The key content and main interventions in iCBT-P has been described in the introduction, but broadly involves gaining and understanding of the factors that maintain perfectionism, experimenting with new ways of thinking and behaving, expanding the source for self-evaluation, and managing self-criticism (Shafran et al., 2016), see Table 2 for an overview. Meanwhile, iUP can be regarded as an emotion-focused treatment that intends to raise awareness of the aversive experiences that an individual has a heightened emotional sensitivity for, and which it then tries to alter or avoid (Ellard et al., 2010). Fundamental to iUP is therefore to register and become more aware of the emotions, cognitions, and physical sensations that occur in difficult situation, and to try out more adaptive ways of coping in these instances. Both iCBT-P and iUP relies on techniques that are commonly used in cognitive behavior therapy. However, one crucial difference is that the former emphasizes knowledge acquisition and refuting dysfunctional beliefs to a great degree, such as by testing out predictions in real life, while the latter leans more toward exposure to emotional stimuli and using mindfulness to shift perspectives in relation to thoughts that evoke strong emotions.

**Table 2 t0010:** Treatment content.

Week	iCBT-P	iUP
1	Understanding your perfectionism, e.g., what is unhelpful perfectionism, what are the pros and cons of perfectionism	Emotional symptoms, e.g., what are emotional symptoms, is this treatment for me, registering your experiences, finding your motivation, setting goals
2	Your own model, values, and motivation, e.g., creating an individual conceptualization on what maintains your perfectionism, cost-benefit analysis	Understanding your emotions, e.g., introduction to emotions, what is an emotion, monitor your emotions

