### Ethics and registration

2.6

The clinical trial has received its ethics approval by the Swedish Ethical Review Authority (Dnr: 2020-01868), and has been registered at ClinicalTrials.gov (NCT04459260). Participants will provide informed consent during the recruitment process and screening. Great consideration will also be made to monitor the condition of those undergoing treatment, i.e., deterioration will be flagged automatically by the secure platform and relevant measures will be taken to ensure further help is introduced (see details under statistical analysis). Meanwhile unwanted and adverse events will also be explored after treatment has ended.

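### Negative effects are measured once, at post-treatment, so participants who leave and also miss that assessment contribute no data on them, and the rate may be under-counted

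*Protocol article*

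**What the plan says.** Section 2.4 (Self-report measures) gives the NEQ its purpose, saying that it "will be used to probe for unwanted and adverse events that might arise during treatment", and adds that it sorts incidents by whether treatment or something else caused them. The same section sets the timing: "the NEQ, which is only filled out at post-treatment". Table 1 agrees, with one mark for the NEQ, under Post. Section 2.6 (Ethics and registration) repeats that "unwanted and adverse events will also be explored after treatment has ended". On analysis, section 2.4 says the instrument "is mainly used to descriptively determine the occurrence and nature of possible negative effects".

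Four other parts of the article bear on harm:
- **Section 2.1:** a weekly PHQ-9, with an alert to the therapist if a participant deteriorates.
- **Section 2.3 (Withdrawal):** on a participant who leaves, "The reason for this will be explored for research purposes, but the individual will be informed that she can defer from specifying her motive".
- **Section 2.8:** counts of reliable deterioration, using the reliable change index.
- **Section 2.9:** 24 interviews after post-treatment, with participants chosen on recovery, non-response or deterioration.

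**The concern.** A harms measure taken only at the end is answered by those still in contact at the end. People who had a bad experience may be over-represented among those who are not. If so, the descriptive NEQ result describes the people who answered, and it will be read as a rate for everyone treated.

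The article itself expects losses. Section 1.1 says perfectionism can lead to "poorer therapeutic alliance, non-response, and drop-out, particularly with regard to the engagement with certain interventions, such as exposure to fearful stimuli", and section 2.8 plans a comparison of completers with non-completers. The trial also sets out to compare two treatments, so a loss that differed between arms would carry into any statement about which one produced more negative effects.

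**Working it through.** **1. Does anything else record treatment-attributed negative effects?**
- The weekly PHQ-9 measures depression and triggers contact. It does not record a cause.
- Reliable deterioration is a change in score, defined alongside recovery on the CPQ. It is not an attributed event.
- The reason for withdrawal is asked, but the participant may decline to give it.
- The interviews cover 12 people per arm, take place after post-treatment and are selected on results, so they are unlikely to reach those who left.

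Each is useful, but none replaces the NEQ.

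**2. Can the stated missing-data method fill the gap?** Section 2.8 ties multiple imputation to the repeated measures analysis of variance. A measure taken once cannot enter that analysis, and the NEQ is described as mainly descriptive. On the stated plan, a missing NEQ stays missing.

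**3. How large could the under-count be?** The article gives no figure to reproduce on this point. Its sample size does reproduce: a two-sided t-test with d = 0.50, alpha 0.05 and power 0.80 needs 63.77, so 64 per arm. It matters here only as the number per arm. All rates below are assumptions.

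Let m be the share missing the NEQ, with negative effects in 20% of those who answer and 50% of those who do not.

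True rate = (1 − m) × 0.20 + m × 0.50; reported rate = 0.20.

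| m | True rate | Reported |
|---|---|---|
| 0.10 | 0.18 + 0.05 = 23% | 20% |
| 0.20 | 0.16 + 0.10 = 26% | 20% |
| 0.30 | 0.14 + 0.15 = 29% | 20% |

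At m = 0.20 and 64 per arm, 12.8 people are missing, and 12.8 × 0.50 = 6.4 affected people per arm go unseen. This scenario implies that 0.10/0.26 = 38% of affected people miss the NEQ, against 0.10/0.74 = 14% of unaffected people.

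**4. When is the comparison between arms affected?** Take the same true rate p in both arms, with shares a of affected and u of unaffected people missing the NEQ.

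Reported rate = p(1 − a) / [p(1 − a) + (1 − p)(1 − u)], with u = 0.10 throughout.

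| p | a, iCBT-P | a, iUP | Reported, iCBT-P | Reported, iUP | iUP minus iCBT-P |
|---|---|---|---|---|---|
| 0.20 | 0.30 | 0.30 | 16.3% | 16.3% | 0 |
| 0.30 | 0.30 | 0.30 | 25.0% | 25.0% | 0 |
| 0.20 | 0.20 | 0.40 | 18.2% | 14.3% | −3.9 points |
| 0.30 | 0.20 | 0.40 | 27.6% | 22.2% | −5.4 points |

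With equal loss, and the same true rate in both arms, both arms are under-counted and no false difference appears. A false difference needs unequal loss. In the last two rows it makes iUP look safer than it is.

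**The case against.** The strongest reply is that stopping treatment is not the same as missing the assessment. Nothing in the article excludes people who stop the modules from the post-treatment questionnaires, and the NEQ asks about events during treatment, so one later administration still covers earlier events for anyone who answers. That stands. A reader might infer that people who leave because of negative effects are simply not counted. The documents support only that they contribute no NEQ data if they also miss post-treatment.

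A reader might also infer that the plan itself implies heavier loss in iUP, since section 1.1 links perfectionism to drop-out around exposure and section 2.5 says "the latter leans more toward exposure to emotional stimuli". The documents do not go that far:
- The sentence in section 1.1 concerns engagement and drop-out in general, not drop-out caused by negative effects.
- It goes on to name behavioral activation, and iCBT-P includes behavioral experiments and pleasurable activities (Table 2, week 3).
- Section 2.5 says the interoceptive exposure module was removed from iUP, although Table 2 still lists exposure to bodily sensations in week 6. Those two statements need reconciling.
- The Abstract calls the difference in adherence unknown.

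A third tempting reading is that the Discussion promises negative-effects data to 12 months. Its sentence names perfectionism, psychiatric symptoms, self-compassion and quality of life, not negative effects.

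Finally, the trial could not resolve a modest difference in harms even with complete data. For 23% against 29% with 64 per arm, the standard error is √(0.23 × 0.77/64 + 0.29 × 0.71/64) = 7.7 points, a 95% interval of about ±15 points. That is fair, and it is why the point rests on the under-count rather than on the contrast between arms.

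**Conclusion.** The point holds as a limited weakness in a stated schedule. Sections 2.4 and 2.6 and Table 1 agree with each other, so there is no contradiction. They place the only treatment-attributed harms measure where people who leave are most likely to be absent, and nothing else in the article stands in for it. The under-count requires only that affected people are likelier than others to miss post-treatment, which is plausible but not shown. Distortion between arms requires in addition that this loss differs by arm, for which sections 1.1 and 2.5 give a reason but no evidence.

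The true size is unknown. The 20% reported against 26% true, and the false gaps of about 4 to 5 points, rest wholly on assumed rates. This is a worthwhile, inexpensive improvement and not a flaw that threatens the trial's main results.

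**What to change.** 1. Have the platform send the NEQ automatically when a participant withdraws or is referred out.
2. State that the post-treatment NEQ is still requested from everyone who stopped the modules.
3. Report negative effects by arm, beside the number randomised and the number with no NEQ at all.

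This needs a change to Table 1, platform scheduling and a reporting rule. It needs no extra staff and changes no treatment, eligibility criterion or sample size. The cost is one additional voluntary 32-item online questionnaire for those who leave. Some will not answer, so the under-count is reduced rather than removed, and item 3 lets the reader see what remains.

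Adding the NEQ at 6 and 12 months is optional. It would show persistent or late effects, which the article does not undertake to report. An extra NEQ during treatment is not needed for this purpose, and one placed before week 6 could not record effects of the iUP exposure modules in weeks 6 and 7.
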